### Data analysis

We will start by examining the characteristics of the study sample, including the prevalence of coexisting physical and mental health conditions, levels of disturbance in work and social functioning, quality of life, and actions taken to try to avoid catching COVID-19 using simple descriptive statistics. For the cohort study, we will examine the proportion who remain above threshold for severe COVID-19 anxiety (9 or above on the CAS) and for COVID-19 anxiety (5 or more on the CAS) at 3 and 6 months after completion of the baseline survey. We will examine factors that influence changes in CAS scores over this period using linear regression analysis. The analysis will be performed in two stages. Initially, the separate association between each factor and CAS at each outcome timepoint will be assessed separately. CAS Score at baseline will be included in all these analyses, as the inclusion of this factor will mean that the analyses reflect factors associated with change in CAS from baseline. The second stage of the analysis will examine the joint association between the factors and CAS Score in a multivariable analysis. To restrict the number of variables in this stage of the analysis, only factors showing some association with the outcome (p<0.2) from the first stage of the analysis will be considered in the multivariable analyses. A selection procedure (eg, backwards selection) will be considered to identify factors significantly associated with the outcome and to be included in the final model.

We anticipate that there will be little missing data because the platform we designed for data entry requires participants to complete every item of a questionnaire before moving on to the next section. However, where the number of missing items on a given measure is 20% or less, then the missing value for the items will be substituted by the individual’s mean score for the remaining items on the scale. If there are more than 20% missing items in the scale the outcome measure will not be calculated for the participant at that time point.

Our criteria for determining the success of the feasibility study, which are based on thresholds used in other recent feasibility and pilot studies,^52 53^ are: recruitment of at least 32 participants (80% of the target study sample of 40 participants), uptake of the intervention by at least 60% of participants in the active arm of the trial, and completion of follow-up interviews at 6 months by 75% of study participants. All data will be analysed in SPSS V.2.0 and Stata V.16.1.^54^

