The link between health anxiety and poor mental health seen in previous pandemics is important because health anxiety is treatable. Cognitive–behavioural therapy for health anxiety (CBT-HA) leads to long-term reductions in levels of health anxiety, generalised anxiety and depression.^29 30^ In recent years, the intervention has been successfully modified to enable it to be delivered remotely.^31^

As social distancing measures are relaxed and people are able to resume social and occupational roles, it is essential to understand the course and consequences of severe COVID-19 anxiety and examine interventions that could improve people’s mental health and functioning. However, at this stage, we do not know the course of COVID-19 anxiety or the contribution that health anxiety plays in maintaining it. While CBT-HA is effective under normal circumstances, we need to find out if it is an appropriate intervention to offer during a global pandemic, when people continue to be asked to be vigilant in spotting the signs of infection in an effort to prevent transmission of the virus.

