**Figure 1 F1:**
[figure not shown]
Study flow diagram. CBT-HA, cognitive–behavioural therapy for health anxiety; sHAI, Short for of Health Anxiety Inventory; TAU, treatment as usual.

We identified potential participants for the feasibility trial from their responses to the baseline survey. We aimed to recruit participants according to the capacity of study therapists to deliver CBT-HA to those in the active arm of the trial. When therapists had capacity to work with more people, we emailed those who recently joined the cohort study and met the additional eligibility criteria a copy of an additional participant information sheet and directed them to an online consent form (see online supplemental file 2). A researcher contacted these participants by telephone to answer any queries they had about the study, confirm that they met study eligibility criteria, support them to complete the online consent form and countersign it. The researcher then contacted the trial manager who randomised the participant. Any participant who was approached to take part in the randomised trial and was ineligible or declined to take part, remained in the cohort study and will be asked to complete subsequent follow-up surveys.

10.1136/bmjopen-2021-059321.supp2Supplementary data

Following attempts by what appeared to be automated survey-takers or ‘bots’ to take part in the study, we added a CAPTCHA question and a ‘trap’ question.^34 35^ The ‘trap’ question provided a range of valid and non-valid but plausible options for how the potential participant had heard about the study, with only those providing a valid response being invited to complete the baseline survey.

Between February 2021 and September 2021, we recruited 306 participants to the study. Of these, 127 (41.5%) met inclusion criteria for the feasibility trial. Among 108 participants offered a place on the trial, 40 (37.0%) accepted and were randomised. The total sample for the cohort study is 285 comprising 179 who were ineligible for the trial, 19 who were eligible but not offered a place due to limited capacity of therapists to take on new patients, 68 who were offered a place on the trial but declined it and 19 people who were randomised to treatment as usual.

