#### Baseline assessment and covariates

At baseline, we collected self-reported data on demographic factors (age, gender, ethnicity, household composition, occupational status), physical health (current medical conditions) and exposure to COVID-19 (whether they had had COVID-19, whether they had been admitted to hospital with COVID-19). We asked participants whether they live with or care for someone that might get seriously ill if infected with COVID-19 because of their health or age and whether someone in their family or a close friend had been in hospital with COVID-19.

We also asked participants questions about behaviours intended to reduce the risk of exposure to COVID-19. These questions were developed with the help of the members of the Lived Experience Advisory Panel and covered five behaviours which people had used or heard of others using in an effort to avoid catching COVID-19: staying at home, avoiding shops, washing or discarding letters and parcels, increased handwashing and increased washing of clothes. People who lived with school age children were also asked whether they had stopped them attending school because of concerns about COVID-19.

We assessed self-reported functioning using the Work and Social Adjustment Scale^37^ and health-related quality of life using the European Quality of Life 5 Dimensions - 3 Levels (EQ-5D-3L).^38^ We assessed mental health using the Patient Health Questionnaire-9,^39^ Generalised Anxiety Disorder 7-item scale,^40^ Obsessive–Compulsive Inventory—Revised,^41^ the short form of the Health Anxiety Inventory (SHAI),^33^ the Standardised Assessment of Personality—Abbreviated Scale (SAPAS),^42^ the DPQ,^43^ use of alcohol (Alcohol Use Disorders Identification Test - Concise (AUDIT-C))^44^ and a single-question screening test for drug use.^45^ Finally, we asked participants to indicate admissions to hospital, contacts with primary and secondary care services using items from the adult service user schedule.^46^

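### The factor models name no term for date of entry, so factors that vary with calendar time may be confounded by changing pandemic conditions when objective 3 is answered

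*Protocol article*

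**What the plan says.** The Data analysis section plans linear regression of follow-up CAS in two stages.

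- **Stage 1** takes factors one at a time: "the separate association between each factor and CAS at each outcome timepoint will be assessed separately". On covariates it says: "CAS Score at baseline will be included in all these analyses".
- **Stage 2** is joint: "The second stage of the analysis will examine the joint association between the factors and CAS Score in a multivariable analysis". Entry to it is by a screen: "only factors showing some association with the outcome (p<0.2) from the first stage of the analysis will be considered in the multivariable analyses". Backwards selection may follow.

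The Recruitment and follow-up section gives the entry period: "Between February 2021 and September 2021, we recruited 306 participants to the study". The Follow-up surveys section times both surveys from each participant's own baseline. The Introduction places the study in a period of change: "As social distancing measures are relaxed and people are able to resume social and occupational roles".

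The Baseline assessment and covariates section lists demographic factors, physical health, previous COVID-19 and hospital admission for it, and behaviours including "staying at home, avoiding shops, washing or discarding letters and parcels". It also asks whether school-age children had been kept at home. Date of entry does not appear there, in Table 1 or in the Data analysis section.

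**The concern.** With entry spread over as many as eight calendar months, two people at the same study month can be about seven calendar months apart. They may have answered under different restrictions, infection levels and news coverage.

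Confounding by date needs two links.

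- **Date to factor.** How much people stay at home, avoid shops or keep children off school can change as rules change. The share who have ever had COVID-19 can only grow within a fixed population.
- **Date to outcome.** The CAS asks about symptoms set off by thoughts and news of COVID-19. The Introduction itself connects anxiety to media coverage and to uncertainty about where the pandemic is heading.

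Both links are plausible on the article's own account. Objective 3 and the Discussion give the factor analysis an explanatory purpose: what shapes and maintains the anxiety. A factor that mainly marks early or late entry could be reported as an influence on recovery.

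**Working it through.** **The plan's own figures.** The point disputes no stated number, but the cohort figures set the sample for the check.

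- Cohort: 179 + 19 + 68 + 19 = 285, as stated.
- Analysable at 6 months: 285 × 0.75 = 213.75, stated as 213.
- Precision: 1.96² × 0.15 × 0.85 / 0.05² = 195.9, so 196, as stated.

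**Check 1: size in CAS points.** The documents give no prevalence by month and no CAS trend, so every input here is an assumption.

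Take eight equal entry months, scaled as u = 0, 1/7, …, 1. A behaviour's prevalence moves linearly from a to b. Follow-up CAS, given baseline CAS, falls linearly by d points from the first to the last entry month. The behaviour has no effect of its own and is unrelated to baseline CAS. The apparent difference between people with and without it is then

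d × (a − b) × Var(u) / [p̄(1 − p̄)],

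where p̄ = (a + b)/2 and Var(u) = (8² − 1)/(12 × 7²) = 63/588 = 0.107. In every case below p̄ = 0.6, so p̄(1 − p̄) = 0.24.

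| a to b | d | Calculation | Spurious difference |
|---|---|---|---|
| no trend in prevalence, or d = 0 | – | one factor is zero | 0 |
| 0.7 to 0.5 | 2 | 2 × 0.2 × 0.107 / 0.24 | 0.18 |
| 0.8 to 0.4 | 2 | 2 × 0.4 × 0.107 / 0.24 | 0.36 |
| 0.8 to 0.4 | 4 | 4 × 0.4 × 0.107 / 0.24 | 0.71 |
| 0.9 to 0.3 | 4 | 4 × 0.6 × 0.107 / 0.24 | 1.07 |

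For scale, the two CAS thresholds in the plan (9 and 5) are 4 points apart.

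**Check 2: error rates at the planned size.** This is a simulation with n = 213 and 4,000 runs per cell. A factor with no true effect has correlation r with entry date. Entry date has a standardised linear effect g on follow-up CAS. The coefficient of baseline CAS is 0.4. All three values are assumptions. The model contains the factor and baseline CAS, as in stage 1.

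| r | g | Mean bias (SD units) | Passes p<0.2 | p<0.05 |
|---|---|---|---|---|
| 0 (any g), or g = 0 (any r) | – | about 0 | 19–21% | 4.6–5.6% |
| 0.1 | 0.1 / 0.2 / 0.3 | 0.01 / 0.02 / 0.03 | 20 / 22 / 26% | 5.4 / 6.3 / 8.3% |
| 0.3 | 0.1 / 0.2 / 0.3 | 0.03 / 0.06 / 0.09 | 25 / 38 / 57% | 7.6 / 15.3 / 29.9% |
| 0.5 | 0.1 / 0.2 / 0.3 | 0.05 / 0.10 / 0.15 | 33 / 62 / 87% | 11.9 / 35.3 / 68.4% |

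The mean bias is close to r × g, so it matters only when both links are appreciable.

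**After the fix.** With a linear date term added, mean bias is about 0 in every cell. The null factor reaches p<0.05 in 4.5–5.8% of runs and passes p<0.2 in 19–21%. The simulated date effect is itself linear, so this shows that a correctly shaped term works. It does not show that a straight line suffices for real data.

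**Would listing date as one more candidate be enough?** Not under the stated rule. Stage 1 tests factors singly, so every other factor would still be screened without date. At stage 2, date could fail the p<0.2 screen or be removed by backwards selection.

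**The case against.** The strongest reply is that this is an omission in a condensed article. The text does not say that baseline CAS is the sole covariate, gives no closed list of factors, and would allow entry date to be added in an analysis plan that is not shown. That much stands: the article states nothing false here. It does not settle the matter, because the article fixes the screening rule itself, and that rule leaves stage 1 unadjusted for date even if date becomes a candidate.

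A second reply is that the mechanism is assumed. Everyone scored 9 or more at their own entry, whatever the month. Late entrants were severely anxious despite any relaxation, so a general easing of anxiety need not mean a lower follow-up CAS at a given baseline score. Even the direction is open. Washing parcels, clothes and hands need not follow the restrictions either. This stands, and it is why the size must be given as a range starting at zero.

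Three stronger readings are tempting and unsupported:

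- A reader might infer that the models adjust for baseline CAS and nothing else. That is exact for stage 1 only; stage 2 also adjusts for the retained factors, though not for date.
- A reader might infer that objective 3 will be answered with bias. The documents quantify neither the factor–date link nor the date–outcome link.
- A reader might add recruitment route to the affected factors. It is not among the listed baseline covariates; how people heard of the study appears only as a question to screen out automated responses.

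**Conclusion.** The point holds as a risk, not as a demonstrated bias. The stated models force in baseline CAS and name no term for date of entry, although entry spanned February to September 2021 under changing restrictions. Factors that may move with the calendar may therefore be confounded by it.

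The size is unknown. Under the assumed linear trends it runs from 0 through 0.18 to about 1.1 CAS points. In the simulation, the false-positive rate at p<0.05 runs from nominal when either link is absent to 68.4% in the most extreme cell. Both ranges rest wholly on assumed inputs.

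The consequence is confined to the cohort's factor analysis. The feasibility criteria for the nested trial and the sample size are not touched. The change is worth making because it is cheap and the analysis is meant to explain.

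**What to change.** Add to the Data analysis section that date of the baseline survey enters every stage 1 and stage 2 model alongside baseline CAS, as a linear or low-order spline term. State that it is exempt from the p<0.2 screen and from backwards selection. Report the 3- and 6-month proportions above each CAS threshold by early and late entry, so readers can see whether the course differed by date. A full set of month indicators is more than is needed.

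The Abstract names mixed effects logistic regression where the Data analysis section names linear regression. The date term should go into whichever model is used.

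The cost is one to three degrees of freedom with about 213 analysable people, and somewhat wider intervals for factors correlated with date. With a linear term the standard error is multiplied by about 1/√(1 − r²), before any gain from lower residual variance: 1.05 at r = 0.3 and 1.15 at r = 0.5. No new data are needed, assuming survey dates were stored; the online consent form was dated.

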#### Sample size

We aimed to recruit sufficient numbers of participants to the cohort study in order to randomise 40 participants to the feasibility trial, which is a typical size for such a trial.^50^ A sample of 40 participants would enable us to detect study consent and intervention completion rates of 50%, with 95% CIs of ±11% and ±15%, respectively.

Assuming a rate of follow-up at 6 months of 75%, our cohort of 285 study participants will generate valid data on 213 people. A sample of 196 participants in the cohort study will enable us to estimate a remission rate of 15%±5%, with 95% CI.^51^

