Our reliance on remote methods for recruitment and following up study participants may have limited our ability to develop a rapport with them and this could, in turn, affect our response rate.^55^ We will keep in touch with study participants by email and offer people an honoraria to complete the follow-up surveys in an effort to minimise loss to follow-up.

While the nested clinical trial is large enough to examine the feasibility of a future explanatory trial of CBT-HA for people with severe COVID-19 anxiety it has not been powered to examine the clinical effectiveness of this intervention.

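### The missing-data rule covers skipped items only, while the sample size assumes about 25% of the cohort returns no 6-month survey; as written, the cohort proportions describe responders

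*Protocol article*

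**What the plan says.** The protocol article deals with missing data in two places.

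- **Sample size.** "Assuming a rate of follow-up at 6 months of 75%, our cohort of 285 study participants will generate valid data on 213 people". The precision claim rests on that figure: "A sample of 196 participants in the cohort study will enable us to estimate a remission rate of 15%±5%, with 95% CI". A 75% completion rate at 6 months is also one of the feasibility success criteria at the end of Data analysis.
- **Data analysis.** "We anticipate that there will be little missing data because the platform we designed for data entry requires participants to complete every item". Two rules follow. The first is that "where the number of missing items on a given measure is 20% or less, then the missing value for the items will be substituted", using the person's own mean on the remaining items. The second is that, above 20%, "the outcome measure will not be calculated for the participant at that time point".

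The same section gives the cohort analyses. For the outcome, "we will examine the proportion who remain above threshold for severe COVID-19 anxiety (9 or above on the CAS", with a second cut-off of 5, at 3 and 6 months. For predictors, "We will examine factors that influence changes in CAS scores over this period using linear regression analysis". Each outcome timepoint is analysed separately, always with baseline CAS in the model. The Abstract instead names mixed effects logistic regression for the predictors.

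The risk to follow-up is acknowledged. The Discussion says that limited rapport arises from remote methods and that "this could, in turn, affect our response rate". The stated countermeasures are reminders, researcher contact for trial participants, and a £20 voucher for the 6-month survey.

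**The concern.** The loss that the plan expects is whole surveys, and the loss that it provides for is single items. A reason that applies to items is given for expecting little missing data, and no treatment is stated for the quarter of the cohort assumed to be absent at 6 months.

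This matters most for the proportion still above threshold, which answers the objective on the course of severe COVID-19 anxiety. It is a plain proportion with no adjustment, so it describes the 285 only if responders and non-responders remit at similar rates. It is plausible that answering an emailed survey depends on how anxious the person currently is, but the documents offer no evidence on the direction or strength of such a link. A confidence interval based on the number of responders carries none of that uncertainty.

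**Working it through.** **Inputs from the protocol article.** Cohort 285, follow-up 75%, expected completers 213, target 15% ± 5 points with a 95% interval, required n = 196 (all from Sample size).

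**Input not in the documents.** The remission rate among those lost. It is treated as an assumption and varied.

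**1. Reproduce the plan's figures.**
- n = 1.96² × 0.15 × 0.85 / 0.05² = 195.9, so 196. This agrees.
- 285 × 0.75 = 213.75, stated as 213. This agrees.
- Half-width at n = 196: 1.96 × √(0.15 × 0.85 / 196) = 5.0 points.
- Half-width at n = 213: 1.96 × √(0.15 × 0.85 / 213) = 4.8 points.

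The sample-size arithmetic is sound.

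**2. Expected survey-level loss.** 285 − 213 = 72, and 72 / 285 = 25.3%.

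**3. Bias of the responder-only proportion.** Bias = fraction missing × (remission in responders − remission in non-responders).

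| Assumed gap (points) | Bias (points) |
|---|---|
| 5 | 0.05 × 72/285 = 1.3 |
| 10 | 0.10 × 72/285 = 2.5 |
| 20 | 0.20 × 72/285 = 5.1 |

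The size is the same whether one reports remission or its complement, the proportion still above threshold.

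**4. Direction.** Suppose responders show 15%.
- If those lost do worse, the most the estimate can be too high is 0.15 × 72/285 = 3.8 points, when none of them remit.
- For the estimate to be about 5 points too low, about 35% of those lost would have to remit: (0.35 − 0.15) × 72/285 = 5.1 points.
- An overstatement of 5 points needs a higher responder rate. With 20% in responders and 0% in those lost, the cohort rate is 0.20 × 213/285 = 14.9%, about 5 points below the responder figure.

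**5. Logical limits with 15% observed in 213.**
- None of the 72 remit: 0.15 × 213 / 285 = 11.2%.
- All of the 72 remit: (0.15 × 213 + 72) / 285 = 36.5%.

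These are the limits of what the data could allow, not a forecast.

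**6. Reach of the prevention measures.** Recruitment and follow-up gives everyone automated emails and reminders, but reserves researcher contact for trial participants. Of the 285, 179 + 19 + 68 = 266 were not randomised and fall outside that extra step.

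No 3-month follow-up rate is stated, so the sizes above apply to 6 months only.

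**The case against.** **The two sections need not contradict each other.** Read in context, the sentence about little missing data most naturally concerns items within a survey, and the rules after it are about items. Loss of whole surveys is allowed for in the sample size, with 213 expected against 196 needed. A reader might infer an outright contradiction, and the text does not force that reading. On the milder reading, however, the missing-data paragraph says nothing about the main loss the plan expects, and the allowance in the sample size protects precision, not representativeness.

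**An article may leave imputation details to a fuller document.** This is fair for detail. Here the article does fix an expectation, a reason, a rule and the analyses, and following them gives complete-case results.

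**The abstract names a mixed model.** Mixed effects logistic regression could use 3-month data from people lost at 6 months, under missing at random. That is a real counterpoint. But the body specifies linear regression by timepoint, the abstract applies the mixed model to predictors and not to the proportions, and such a model recovers no follow-up information on people lost at both waves.

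**Baseline CAS is in every regression.** This stands. If non-response depends only on baseline severity and the model is correctly specified, the complete-case coefficients are not biased by it. A reader might infer that the factor estimates are compromised in the same way as the proportions; the documents do not support that. The coefficients are exposed only if response depends on later anxiety given the covariates, or on predictors left out.

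**Follow-up risk is disclosed and mitigated.** This is true, but reminders and vouchers are prevention and do not determine how those still lost are analysed.

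**Conclusion.** The point holds in a limited form. The stated missing-data rule addresses a problem that forced completion already makes rare and leaves the assumed 25% survey-level loss without any stated handling. As written, the threshold proportions at 3 and 6 months and the body's regressions rest on responders.

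A reader might infer that the remission estimate will be wrong by as much as its stated ±5%. That needs a gap of about 20 points between responders and non-responders, a figure found nowhere in the documents. More modest gaps of 5 to 10 points give 1.3 to 2.5 points, less than or about half the sampling half-width of 4.8. So a bias comparable with the interval is possible but not shown to be likely.

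The conclusion rests on the plan's own 75% follow-up, on the Data analysis section being applied as written, and on an assumed gap. Nothing in the sample-size calculation is wrong and the study is not invalidated. The change should be made because the cohort's main descriptive result is affected and the remedy is cheap.

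**What to change.** 1. Limit the sentence on little missing data to items within returned surveys, and state that about 25% survey-level loss is expected at 6 months.
2. Reconcile the Abstract and Data analysis on one regression approach, preferably a repeated-measures model using both follow-up waves.
3. Estimate the 3- and 6-month proportions at or above each CAS threshold by multiple imputation or inverse-probability weighting with baseline covariates, adding 3-month CAS for the 6-month estimate. Report the complete-case figure alongside.
4. Add a sensitivity range that varies remission among non-responders.
5. Minor: exclude EQ-5D-3L from item-mean substitution. One of its five dimensions is exactly 20%, so the rule applies, and a mean level such as 1.25 (from levels 1, 1, 1 and 2) may have no index value. This has no bearing on the remission estimate.

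The cost is revised wording, modest extra analysis and possibly somewhat wider intervals. The screening, baseline and 3-month measures needed are already in the assessment schedule.
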